**Interventions**: (A). GMI intervention: teamleaders of the financial service will be trained to become a GMI-coach. After the two-day training, they will lead a GMI-group, consisting of their own employees. GMI will be applied for 3 sessions of 90 minutes each, over a period of 6 weeks, and will end with a follow-up meeting of 90 minutes, 2 months after the final session. The GMI groups will be supported by a social media platform. Employees will be stimulated through this platform to join physical and relaxation activity groups. (B). Environmental modifications: changes in the physical environment will be made to facilitate daily physical activity and relaxation at work, such as redesigning the coffee corners and the meeting rooms. The control group will receive no specific interventions and will proceed working as usual. A special VIP page will be created on the intranet for all employees, summing up the current offers of the financial service provider which are related to stimulating daily physical activity and relaxation. Furthermore, every two months, all employees will receive a newsletter about the VIP project.

**Main study parameters/endpoints:** Primary outcome measure of the study is need for recovery. Secondary outcome measures are daily physical activity, sedentary behaviour and relaxation/detachment. Furthermore, general health and work-related factors, such as exhaustion, sleep quality, stress, productivity and absenteeism will be measured. In addition, a subsample of 100 employees will be asked to wear an accelerometer for one week during the three measurement periods to measure sedentary and daily physical activity behaviour objectively.

**Hypothesis/anticipated results:** We hypothesize that the VIP program will significantly lower the need for recovery in office employees by increasing daily physical activity and relaxation, compared to the control group, both at short-term (6 months) and long-term (12 months) follow-up.

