# 3.3 Design

In this study, a randomized controlled trial design will be employed, with pre-stratification on environmental modifications. That is, two strata will be created, with (6 wings) and without (7 wings) environmental modifications. Within each stratum, wings will be randomly assigned to GMI or no GMI. Randomisation will take place at wing level. We decided to apply cluster randomisation on wing level to avoid contamination with employees in the control group. Consequently, the study will consist of four research arms, i.e. (1) both GMI and the environmental modifications, (2) environmental modifications/no GMI, (3) GMI/no environmental modifications, (4) no GMI/no environmental modifications (control group). The design of the VIP project is shown in appendix 1.

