# 4.4.2 (B). Environmental modifications

Environmental modifications will be applied to two departments (six wings). The environmental modifications will focus on facilitating daily physical activity and relaxation in the work environment, by changing the coffee corners, the open office environment, the meeting rooms and the entrance hall. Coffee corners will be adapted by adding bar chairs, magazines on the tables, an electronic dartboard, indoor plants, relaxing lights and by painting the coffee corner walls. In addition, the open office environment will be changed by introducing exercise balls, standing desks, sound masking to reduce background noise, and indoor plants. The interior of the meeting rooms will be changed by placing a stand-up table, a lamp, an indoor plant and by painting the walls. Furthermore, a ping-pong table and an indoor plant will be placed in the entrance hall. Prompts of decisions posters to promote daily physical activity and relaxation will be attached on the walls of the coffee corner and the entrance hall. In addition, food steps will be placed on the floor by the entrance hall to promote stair walking. All these environmental modifications will be promoted by posters in the coffee corner and in the hallway. Furthermore, the employees and the teamleaders will receive information by email about the environmental modifications.

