# 6. Statistical analysis

First of all, baseline characteristics will be analyzed on differences between the four intervention arms, by two-way analysis of variance for numerical data and chi-square and logistic regression for categorical data. Multilevel regression analyses will be performed regarding the effectiveness of the intervention on need for recovery, the secondary outcome measures physical activity/relaxation and other work and health-related variables after 6 months (short-term) and 12 months (long-term). The intervention effect will be estimated in each stratum and a pooled estimated effect is calculated across strata. Multilevel analysis takes into account the clustering of observations of employees within the same wing. All analyses will be performed crude, and adjusted for possible confounders, such as gender and age. Also, these variables will be checked for effect modification. Correction for baseline values will be applied. Analyses will be carried out to test differences in sick leave between the four study intervention arms. All statistical analyses will be performed according to the intention-to-treat principle. Per protocol analyses will be performed to investigate the effects of the intervention in participants who showed high compliance (>70%) to the GMI intervention. Where necessary, missing data will be imputed using multiple imputation techniques. For all analyses a two tailed significance level of p<0.05 is considered statistically significant. All analyses will be performed with SPSS 19.0 (SPSS Inc. Chicago, Illinois, USA).

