# 6.1 Economic evaluation

The aim of the economic evaluation will be to determine the cost-effectiveness, from a societal and company perspective, of the three intervention arms in comparison with the control group. Furthermore, the cost-utility from the company perspective will be studied. The follow-up will be one year, similar to the trial. The analyses will be performed according to the intention-to-treat principle. Productivity losses, i.e. sick leave and productivity data, will be measured with the Dutch version of the WHO-HPQ and IWPQ, (see secondary outcome measures), and the company registrations. In addition, participants are asked to complete a retrospective questionnaire, measuring health care use and personal costs related to the intervention. All questionnaires will be administered on a three-monthly basis. First, societal costs and company costs will be estimated, and compared between the intervention group and control group. Also, a cost-benefit analysis (CBA) will be performed in which the incremental intervention costs are compared to the incremental costs for productivity losses. Confidence intervals (95%) around the difference in costs will be obtained by bias corrected and accelerated (Bca) bootstrapping. Subsequently, a cost-effectiveness analysis (CEA) will be performed from the company perspective. An incremental cost-effectiveness ratio will be calculated, by dividing the difference between the mean company costs of the four intervention arms by the difference in the mean effects on the primary outcomes of the four intervention arms. Bootstrapped incremental cost-effectiveness ratios will be graphically presented on cost-effectiveness plans. Cost-acceptability curves will be generated, showing the probability for cost-effectiveness of the intervention at different ceiling ratios. Similarly, the CEA from the societal perspective will compare the incremental societal costs with the incremental effects on the primary outcomes. Sensitivity analyses will be done to assess the robustness of the results.

#

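### Sick leave is to be compared between the four arms, although only GMI is randomised; the randomised, stratified GMI contrast should be named as its main analysis

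*Protocol*

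**What the plan says.** Section 6 of the Protocol (Statistical analysis) plans multilevel regression, with employees clustered in wings, for need for recovery, "the secondary outcome measures physical activity/relaxation and other work and health-related variables after 6 months (short-term) and 12 months (long-term". The contrast for these outcomes is stated: "The intervention effect will be estimated in each stratum and a pooled estimated effect is calculated across strata". Because the strata are defined by environmental modification, the effect within a stratum can only be GMI against no GMI.

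Sick leave then has a sentence of its own: "Analyses will be carried out to test differences in sick leave between the four study intervention arms". It names no model, no role for the stratum and no handling of wings.

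Section 3.3 (Design) describes the allocation: "two strata will be created, with (6 wings) and without (7 wings) environmental modifications". It continues: "Within each stratum, wings will be randomly assigned to GMI or no GMI". Section 4.4.2 says how the environment strata arise: "Environmental modifications will be applied to two departments (six wings". No random assignment of the modifications is described.

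**The concern.** A comparison of four arms has three independent contrasts: GMI, environment, and their interaction. Randomisation by wing within stratum protects the GMI contrast, and also the difference between strata in the GMI effect. It does not protect the environment contrast, which sets two whole departments against the others. Departments may differ in type of work, management and absence habits for reasons unrelated to the programme. A four-arm difference in sick leave could come from that source and still be reported as an effect of the programme. The stratified and pooled analysis avoids this for the other outcomes by comparing wings only within a stratum.

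There is also a possible loss of power. If the four arms are compared in one overall test, a GMI effect is spread over 3 degrees of freedom instead of 1, with only 13 wings to supply the error term. Sick leave also enters the productivity losses in the economic evaluation (section 6.1), so its effect estimate is likely to be used.

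**Working it through.** **The plan's own figure.** Section 3.5 gives no power or effect size for sick leave. Its figure for need for recovery is 260 employees before corrections (difference 12, SD 29.75, power 0.9, two-sided 5%). It reproduces as a two-group comparison: n per group = 2 × (1.960 + 1.282)² × 29.75² / 12² = 129.2, rounded up to 130, so 260 in total. The corrections give 260 × 1.3 = 338, 338 × 0.9 = 304.2 (stated as 305), and 305 / 0.75 = 407, close to the stated 404. The planned size thus rests on one two-group contrast, not on a four-group test.

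**Inputs for sick leave.**
- From the Protocol: 3 GMI and 3 non-GMI wings with modifications, 4 and 3 without (Appendix 1); ICC 0.025 and 404 employees (section 3.5); two-sided 5% (section 6).
- Assumed: the ICC applies to sick leave; 404 / 13 = 31.08 records per wing; outcome in SD units with no allowance for skewness; analysis of wing means; no baseline correction; GMI effects of 0.3 and 0.4 SD; department differences of 0.2 to 0.5 SD. The Protocol gives no SD or effect for sick leave.

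**Precision.**
- Variance of a wing mean: v = 0.025 + 0.975 / 31.08 = 0.0564.
- Information on GMI: 1/(1/3 + 1/3) + 1/(1/4 + 1/3) = 1.500 + 1.714 = 3.214.
- SE of the pooled GMI effect: √(0.0564 / 3.214) = 0.132.

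**Power for a GMI effect d, under three readings.** For the pooled contrast and the two-way main effect, the noncentrality is λ = (d / 0.132)². For one overall test it is λ = d² × (7 × 6 / 13) / 0.0564, as 7 wings have GMI and 6 do not. At d = 0.3 these give 5.13 and 5.16. They are almost equal, so the difference in power comes from the degrees of freedom.

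| Analysis | df | d = 0.3 | d = 0.4 |
|---|---|---|---|
| Stratified, pooled GMI contrast | 1, 10 | 53% | 78% |
| GMI main effect in a two-way analysis | 1, 9 | 52% | 77% |
| One overall four-arm test | 3, 9 | 31% | 52% |

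**No GMI effect, department difference D between strata.** For the overall test, λ = D² × (6 × 7 / 13) / 0.0564 with 3 and 9 df.

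| D (SD) | λ | Overall test significant |
|---|---|---|
| 0.2 | 2.29 | 16% |
| 0.3 | 5.16 | 31% |
| 0.5 | 14.33 | 72% |

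The stratified contrast stays at 5%, because D cancels within strata.

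**Simulation check.** 20,000 runs per setting with 31 records per wing gave power of 78% (stratified) against 53% (overall test) at 0.403 SD, and 40% against 23% at 0.25 SD. With no GMI effect, the overall test rejected in 16% of runs at D = 0.2 and 51% at D = 0.4; the stratified test rejected in about 5%.

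**The case against.** A reader might infer three stronger things that the Protocol does not support.

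- **That a 3-df overall test is planned.** The sentence names no test. For baseline differences between the four arms, the same section uses two-way analysis of variance for numerical data. On that model, GMI is a 1-df effect adjusted for environment, power is practically that of the stratified contrast (52% against 53%), and a department difference falls on the environment factor.
- **That the four-arm test replaces the stratified analysis.** The Summary says that "general health and work-related factors, such as exhaustion, sleep quality, stress, productivity and absenteeism will be measured", and section 6 puts other work and health-related variables under the multilevel model. Absenteeism may therefore already be covered, with the sick-leave sentence as an addition.
- **That sick leave is the only result compared by arm.** The economic evaluation in section 6.1 assesses the cost-effectiveness "of the three intervention arms in comparison with the control group".

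Two further objections have weight. Section 6 also promises correction for baseline values and confounders, which would remove part of a stable department difference; the rejection rates above allow for none of this. Environment is also one of the two programme components, so a four-arm comparison is of legitimate interest and need not be dropped.

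It can also be said that the model for an outcome that is neither primary nor listed as secondary belongs in the SAP. That holds for the distribution and the covariates. It does not dispose of the point: the Protocol itself fixes a comparison for sick leave that differs from the one for its other effectiveness outcomes and crosses strata that were not randomised. If sick leave is to have both analyses, nothing says which is the main one.

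**Conclusion.** The concern holds in a limited form. The stated sick-leave comparison crosses environment strata that consist of whole departments, so a difference between the four arms cannot by itself be attributed to the intervention. This follows from the design and needs no assumed figures. It applies equally to pairwise comparisons of arms in different strata.

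The numerical consequences are conditional. A fall in power from 53% to 31% at 0.3 SD, and significance in about 16% to 72% of trials from a department difference of 0.2 to 0.5 SD alone, apply only if one 3-df test is meant. They also rest on an assumed scale, the Protocol's ICC carried over to sick leave, and no baseline correction. Under a two-way analysis the power loss is negligible, and what remains is the non-randomised environment term and the missing statement of which contrast is the main one. As sick leave is not the primary outcome, this is a worthwhile correction and not a threat to the trial's main conclusion.

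**What to change.** In section 6, replace the sick-leave sentence with one that states:

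- The main sick-leave analysis is GMI against no GMI, from the same multilevel model as the other effectiveness outcomes, estimated in each environment stratum, pooled across strata, and accounting for wing.
- The model uses a distribution suited to day counts.
- Any comparison of the four arms, or of environmental modification against none, is secondary and labelled as not randomised across strata.

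This takes a few lines of text and needs no new data or participants. The small price is that a four-arm p-value is no longer the main sick-leave result; the comparison itself can still be reported.

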# 6.1 Economic evaluation

The aim of the economic evaluation will be to determine the cost-effectiveness, from a societal and company perspective, of the three intervention arms in comparison with the control group. Furthermore, the cost-utility from the company perspective will be studied. The follow-up will be one year, similar to the trial. The analyses will be performed according to the intention-to-treat principle. Productivity losses, i.e. sick leave and productivity data, will be measured with the Dutch version of the WHO-HPQ and IWPQ, (see secondary outcome measures), and the company registrations. In addition, participants are asked to complete a retrospective questionnaire, measuring health care use and personal costs related to the intervention. All questionnaires will be administered on a three-monthly basis. First, societal costs and company costs will be estimated, and compared between the intervention group and control group. Also, a cost-benefit analysis (CBA) will be performed in which the incremental intervention costs are compared to the incremental costs for productivity losses. Confidence intervals (95%) around the difference in costs will be obtained by bias corrected and accelerated (Bca) bootstrapping. Subsequently, a cost-effectiveness analysis (CEA) will be performed from the company perspective. An incremental cost-effectiveness ratio will be calculated, by dividing the difference between the mean company costs of the four intervention arms by the difference in the mean effects on the primary outcomes of the four intervention arms. Bootstrapped incremental cost-effectiveness ratios will be graphically presented on cost-effectiveness plans. Cost-acceptability curves will be generated, showing the probability for cost-effectiveness of the intervention at different ceiling ratios. Similarly, the CEA from the societal perspective will compare the incremental societal costs with the incremental effects on the primary outcomes. Sensitivity analyses will be done to assess the robustness of the results.

#

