3.5 Sample size calculation The sample size calculation is based on the main outcome measure, i.e. need for recovery, measured by the need for recovery questionnaire (63). The mean need for recovery score is 27,30 (SD=29,75) according to the validation study of Van Veldhoven et al. (63). Minimal relevant difference on the need for recovery scale, with a range from 0 to 100, was set on 12. This was based on the articles by de Croon et al. (64) and Kuijer et al. (65), in which on average a relevant difference of 12 was found in nurses, truck drivers and refuse collectors, after an intervention, such as change in work hours (64) or job rotation (65). Using a power of 0.9, in total 260 employees are needed. Because randomisation takes place at wing level, a cluster correction was applied. An intraclass correlation (ICC) of about 0.025 is assumed, based on previous studies showing that worksite level ICC’s for health-related outcomes are generally small (66-68). This leads to a cluster correction factor of 1 + (13-1)* 0.025 = 1.3. Based on this cluster correction, a total of 1.3*260 = 338 employees will be needed. Furthermore, by applying a correction for repeated measurement we will win some precision, therefore an additional correction by a factor 0.9 seems justified, resulting in 0.9×338=305 employees in total. Finally, accounting for a loss to follow-up of 25% in twelve months, a total of 404 employees for the four intervention arms will be needed at baseline. Based on the source population of 980 employees (13 wings), the number of 404 employees is reached at a participation rate of 42 percent. This percentage is considered feasible, because all teamleaders and their employees within a wing will be asked to participate.

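### The economic evaluation (section 6.1) sets out a bootstrap and a ratio of mean differences without carrying over section 6's wing clustering and baseline correction, and its comparators need reconciling

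*Protocol*

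**What the plan says.** Protocol section 3.3 randomises wings, not employees. Appendix 1 shows 13 wings split 3, 3, 4 and 3 over the four arms.

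For the effects, section 6 prescribes multilevel regression and explains why: "Multilevel analysis takes into account the clustering of observations of employees within the same wing". It adds "Correction for baseline values will be applied". The outcomes it names for this model are need for recovery, the secondary outcomes, and other work- and health-related variables. Costs are not named. Section 6 also says, in general terms, that all analyses will be done both crude and adjusted for confounders.

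For costs, section 6.1 states: "Confidence intervals (95%) around the difference in costs will be obtained by bias corrected and accelerated (Bca) bootstrapping". Its ratio divides "the difference between the mean company costs of the four intervention arms" by the corresponding difference in mean effects. Bootstrapped ratios then feed the cost-effectiveness planes, and acceptability curves are to be drawn. Section 6.1 restates intention to treat but says nothing about wings, strata or baseline values.

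Section 6.1 describes the comparison in three ways: its aim sets three intervention arms against control, its cost step sets one intervention group against a control group, and its ratio refers to four intervention arms.

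**The concern.** Employees in one wing share managers, workload and, in some wings, the refurbished surroundings, so sick leave and productivity costs may be correlated within wings. A bootstrap that treats employees as independent leaves out the between-wing variance. Its cost intervals are then too short, and the planes and curves look more decisive than a trial of 13 wings allows.

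If the ratio uses raw follow-up means, one report could give a baseline-corrected effect on need for recovery and a cost-effectiveness ratio built on a different effect.

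Four arms have no single difference. The analyst must choose the contrasts, and the three descriptions point to different ones. Cost-effectiveness and cost-utility are stated secondary objectives (section 2), and the company would rely on these results.

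**Working it through.** **1. Reproducing the plan's own figure.** Section 6.1 gives no number, so the inputs come from section 3.5: SD 29.75, ICC 0.025, and "Minimal relevant difference on the need for recovery scale, with a range from 0 to 100, was set on 12". With two-sided alpha 0.05 and power 0.90, the standard two-group formula gives 130 per group, 260 in total, which matches "Using a power of 0.9, in total 260 employees are needed". Then 260 × 1.3 = 338 and 338 × 0.9 = 304.2 (stated as 305). With 25% loss, 305/0.75 = 407 against the stated 404, which is close enough.

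**2. Employees per wing.** At baseline 404/13 = 31.1; on the 305 needed after loss, 305/13 = 23.5.

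**3. Effect of ignoring wings.** Design effect DE = 1 + (m − 1) × ICC, with m employees per wing. An interval that ignores clustering has a standard error too small by the factor √DE. Its coverage is 2Φ(1.96/√DE) − 1. The protocol gives no ICC for costs, so 0.025 is carried over as an assumption and varied.

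| Assumed cost ICC | DE, m = 23.5 | Coverage | DE, m = 31.1 | Coverage |
|---|---|---|---|---|
| 0.005 | 1.11 | 94% | 1.15 | 93% |
| 0.01 | 1.23 | 92% | 1.30 | 91% |
| 0.025 | 1.56 | 88% | 1.75 | 86% |
| 0.05 | 2.12 | 82% | 2.50 | 79% |

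At ICC 0.025, √DE is 1.25 to 1.32, so the intervals are 1 − 1/√DE = 20-24% too short.

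**4. Check by simulation.** BCa intervals from resampling individuals were simulated with skewed costs, 3 against 3 wings and 25 employees per wing. Coverage was 93% at ICC 0 (a small loss with no clustering at all), 90% at 0.01, 86% at 0.025 and 80% at 0.05. With 7 against 6 wings, 24 per wing and ICC 0.025 it was 86%.

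**5. Is resampling whole wings enough?** No. In the same simulation, a plain percentile interval from resampled wings covered about 80% with 3 against 3 wings, and 88% with 7 against 6, at ICC 0.025. A small-cluster correction is needed as well.

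**6. Baseline.** Taking the protocol's SD and ICC and 31 employees per wing, a wing mean has SD 29.75 × √(0.025 + 0.975/31) = 7.07. The chance baseline difference between two arms of 3 wings has SD 7.07 × √(2/3) = 5.8 points, against a target of 12. How much of this reaches an uncorrected follow-up difference depends on the slope of follow-up on baseline, which the protocol does not give. For assumed slopes of 0.3 to 0.7 the SD carried over is 5.8 × 0.3 = 1.7 to 5.8 × 0.7 = 4.1 points.

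**7. Comparators.** Only GMI is randomised, within environmental strata (section 3.3). The modifications are applied to two departments (section 4.4.2). Of the three comparisons with control in the stated aim, GMI alone against control is therefore randomised. The two that involve environmental modifications cross strata and are not.

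**The case against.** Section 6.1 does not say that employees are the resampling unit. BCa names a way of building the interval, not the unit drawn, and such detail is often left to an analysis plan, which is not shown here. A reader might infer that the intervals are certain to be too narrow. The text does not support that; it supports only the conditional statement.

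A reader might also infer that the ratio is bound to carry baseline imbalance, or could have the opposite sign to the reported effect. Section 6.1 is a subsection of section 6, whose general sentences on adjustment and baseline correction may be meant to reach it. No calculation from the documents supports a change of sign.

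Nor is the ratio beyond repair. The aim names three arms against control, and the protocol elsewhere uses four intervention arms as a label for all arms, so pairwise ratios against control are the natural reading. The wording is mostly loose drafting.

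Finally, the ICC of 0.025 is for health-related outcomes. If costs hardly cluster, little is lost.

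What remains is that section 6.1 does not simply leave the method open. It names one for costs and writes a formula in terms of means, while the multilevel model in section 6 is tied to a list of outcomes without costs. An analyst following 6.1 as written, with a standard bootstrap, would drop both features.

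**Conclusion.** The point holds as a gap between sections 6 and 6.1, with a conditional consequence. If employees are resampled individually, nominal 95% cost intervals cover about 86-88% at a cost ICC of 0.025; the loss is small at 0.005 and serious at 0.05. This rests on the planned numbers per wing and on an assumed ICC for costs. The risk of an unadjusted denominator follows from a literal reading of the ratio and is not established. The inconsistent comparators are plain in the text and need reconciling, though the stated aim shows the likely intent. The primary effectiveness analysis is not affected.

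**What to change.** State in section 6.1 that incremental costs and effects are estimated with multilevel models: a random intercept for wing; GMI, environmental stratum and their interaction; and baseline need for recovery in the effect model. Stratum and environmental modification are the same variable here and enter once. Add a small-cluster correction. For scale, a wing-level comparison of 3 against 3 has 4 degrees of freedom, with a critical value of 2.78 rather than 1.96.

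If a bootstrap is preferred, use a two-stage scheme within stratum (wings, then employees), also with a small-cluster correction. Draw the planes and acceptability curves from whichever estimates are used.

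Define each ratio as a named pairwise contrast: each of the three arms against control, as the aim says, plus GMI against no GMI within stratum and pooled. Note that contrasts across environmental strata are not randomised. Use the same wording in the cost step and the ratio sentence.

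The cost is protocol wording, some extra analysis work and wider intervals. No new data are needed.
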